#### For the cost-effectiveness aim

Healthcare resource use will be collected and summarised for each trial arm for inclusion in subsequent cost-effectiveness analyses making comparisons consistent with comparisons made in the primary analyses.

#### Sample size

Based on the primary outcome (exacerbation rate), we want to detect a significant difference between those allocated to erdosteine vs placebo (controls). We will use a negative binomial model (similar to our previous RCT),^19^ and we will have 90% power (alpha=0.05) to detect a 40% reduction in the respiratory exacerbation rate in the erdosteine group (controls=3/year, intervention=1.8/year), if we obtain final endpoint data from 164 persons. To account for a 25% attrition loss, we will enrol a total of 194 people. We conservatively estimated a 40% reduction in respiratory exacerbation rate based on the following: a paediatric study (total n=158) reported an absolute reduction in cough by 47% in those receiving erdosteine^32^ while adults with COPD allocated erdosteine (total n=155) had 58% fewer days in hospital,^27^ compared with placebo.

We postulate superiority between groups for QoL. The minimal clinical important difference for the PC-QoL instrument is 0.9^45^ (SD 1.8) while that of the adult B-QoL tool is domain dependent (7–10) (SD 17).^44^ With the standardisation of the scales, we will have 90% power to detect a difference of means between groups of 0.5 SDs. We are aware our study is insufficiently powered for the other secondary outcomes.

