**Methods and analysis:**

We are undertaking an international multicentre, double-blind, placebo-RCT to evaluate whether 12 months of erdosteine is beneficial for children and adults with bronchiectasis. We will recruit 194 children and adults with bronchiectasis to a parallel, superiority RCT at eight sites across Australia, Malaysia and Philippines. Our primary endpoint is the rate of exacerbations over 12 months. Our main secondary outcomes are QoL, exacerbation duration, time-to-next exacerbation, hospitalisations and lung function.

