### Outcomes and endpoints

Our primary outcome is the acute respiratory exacerbation rate by 12 months postrandomisation. These are collected by participant reports (active surveillance of participants) and medical records.

In children, we will use the definition used previously^18 43^ that is also in accordance with the ERS-based guidelines^2^ and the ERS Task Force international consensus definition of an exacerbation.^3^ For children, an episode is defined by an acute respiratory event that (1) is treated with antibiotics and (2) has an increase in sputum volume and/or purulence, or >3 days of change in cough (at least 20% increase in cough score or change in quality (dry to wet/productive)) or physician-confirmed acute change in respiratory rate, effort or chest signs.^3^ For adults (aged>18 years), we will use the adult consensus definition that is, a clinician determines that treatment change is required and deterioration in ≥3 of the following for ≥48 hours (cough, sputum volume or purulence, breathlessness, exercise tolerance, fatigue and/or malaise, haemoptysis).^24^

Other outcomes (see online supplemental material for further information) are as follows:

10.1136/bmjresp-2023-002216.supp1Supplementary data

QoL scores at 12 months: In adults, we are using the bronchiectasis QoL tool (B-QoL),^44^ which has 37 questions with a respiratory subdomain score. In the absence of a bronchiectasis-specific QoL for children, we are using the validated Parent-proxy Cough QoL-8 instrument (PC-QoL).^45^
Time-to-next exacerbation: Defined from the time of commencing trial medications to the next respiratory exacerbation (defined above), measured in days.Time-to-next respiratory-related hospitalisation.Spirometry values (forced expiratory volume in 1 s (FEV_1_ z-score) and forced vital capacity (FVC) z-score, and FEV_1_/FVC ratios).Adverse events, including gastrointestinal symptoms (eg, nausea, vomiting, abdominal pain, diarrhoea), headaches, rashes, use of additional non-macrolide antibiotics for non-pulmonary infections during the intervention, that is, for 12 months postrandomisation.Healthcare resource use.

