#### For the primary aim

To assess erdosteine efficacy, the exacerbation rate in those randomised to receive erdosteine will be compared with controls (receiving placebo). We will use a negative binomial regression model (as recommended,^46^ including treatment group, and number of months in the study included as an offset) to determine between-group differences (with 95% CI), as done previously.^19^

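### The three sample-size figures (164 evaluable, 25% attrition, 194 enrolled) cannot all be right, and the plan does not show which one is wrong

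*Protocol article*

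**What the plan says.** Under Sample size, the protocol article plans a negative binomial comparison of exacerbation rates, 3 per year on placebo against 1.8 per year on erdosteine (a 40% reduction), with 90% power at alpha 0.05. That power is conditional: "if we obtain final endpoint data from 164 persons". The next sentence gives the enrolment target: "To account for a 25% attrition loss, we will enrol a total of 194 people". The abstract repeats the target: "We will recruit 194 children and adults with bronchiectasis".

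Two other places bear on the point. Outcomes and endpoints fixes the period: "Our primary outcome is the acute respiratory exacerbation rate by 12 months postrandomisation". The section on the primary aim says that the negative binomial model has the "number of months in the study included as an offset". The article gives no dispersion parameter, allocation ratio or sidedness for the test, and no second attrition rate or evaluable number.

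**The concern.** An attrition allowance should link the number needed for analysis to the number enrolled. Here it does not: the stated 25% does not lead from 164 to 194, either by the correct inflation or by the common incorrect one. At least one of the three figures is wrong as written.

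The consequence is practical. A loss of between 15.5% and 25% would look as if it were within plan, yet would leave fewer than the 164 on which the power statement depends. Anyone interpreting a null result needs to know which loss was planned for, particularly as the article already warns, because of the pandemic, that the primary comparison may be underpowered.

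**Working it through.** **Inputs from the Sample size section.** Evaluable number 164; attrition 25%; enrolment 194; rates 3 and 1.8 per year; power 90%; alpha 0.05. Follow-up is 12 months (Outcomes and endpoints).

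**Assumptions, because the article does not state them.** Two-sided test, 1:1 allocation, and a common dispersion k.

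**Step 1: try to reproduce 194.**
- Correct inflation, N/(1 − d): 164/0.75 = 218.7, so 219.
- Common incorrect inflation, N × (1 + d): 164 × 1.25 = 205.
- Neither gives 194, and the gaps of 25 and 11 are too large for rounding.

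**Step 2: work back from 194.**
- Left after a 25% loss: 194 × 0.75 = 145.5, which is 18.5 short of 164.
- Loss that 194 covers: 1 − 164/194 = 15.5%. For comparison, 164/0.85 = 192.9.
- Evaluable number that would fit both 25% and 194: about 146, since 146/0.75 = 194.7.

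**Step 3: power if only completers count.** With n per arm and one year of follow-up, the variance of the log rate ratio is (1/3 + 1/1.8 + 2k)/n. Power is Φ(|ln 0.6|/SE − 1.96).
- Solve for k so that n = 82 gives 90%: 1/3 + 1/1.8 + 2k = 82 × (ln 0.6)²/(1.96 + 1.2816)² = 82 × 0.2609/10.507 = 2.036. Hence k = (2.036 − 0.889)/2 = 0.574.
- At 145.5 in total, n = 72.75 and SE = √(2.036/72.75) = 0.1673. Power = Φ(0.5108/0.1673 − 1.96) = Φ(1.093) = 86.3%.

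**Step 4: separate dispersion from attrition.** Power with the full 164, then with 145.5:

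| k | 164 | 145.5 | Difference |
|---|---|---|---|
| 0.3 | 96.6% | 94.6% | 2.0 points |
| 0.574 | 90.0% | 86.3% | 3.7 points |
| 1.0 | 77.7% | 72.7% | 5.0 points |

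The attrition discrepancy costs 2 to 5 points. The much wider spread down each column comes from the unknown dispersion.

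**Step 5: power when partial follow-up counts.** Take 194 enrolled (97 per arm), 25% lost, and k = 0.574. If those lost contribute a fraction t of a year, the information in an arm with rate μ is 97 × [0.75μ/(1 + kμ) + 0.25μt/(1 + kμt)]. The variance of the log rate ratio is the sum of the reciprocals over the two arms.

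| Mean follow-up of those lost | Power |
|---|---|
| 0 months | 86.3% |
| 1 month | 88.1% |
| 2 months | 89.4% |
| 3 months | 90.4% |
| 6 months | 92.4% |

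**The case against.** The best defence is that the primary analysis is not restricted to completers. It is by intention to treat, participants are contacted monthly, and the offset credits whatever follow-up each one provides. Step 5 shows that 194 enrolled with 25% lost can still give about 90% power. This defence stands against any flat statement that the trial misses its power. It does not repair the text: the Sample size section makes the power conditional on endpoint data from 164 people and does not appeal to partial follow-up.

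A second objection is that 164 need not be the correct anchor. An evaluable number of 146 would fit 25% and 194 almost exactly, and a transposition of digits would explain it. In that case the attrition allowance is sound, and 90% power at 146 would correspond to k of about 0.46. This is conjecture, but the article does not exclude it.

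A reader might therefore infer that the trial is short of its stated 90%, or that the correct statement is 86%. The documents support neither. The 86% rests on a dispersion solved from the disputed 164 and on giving no credit to those who leave early. Nor should power of 73% at k = 1.0 be blamed on attrition, because the full 164 would give only 77.7% at that dispersion.

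**Conclusion.** The inconsistency is certain and needs no assumption: 164, 25% and 194 are incompatible, by about 18 evaluable participants or 25 enrolled. Which figure is wrong cannot be settled from the article.

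The effect on power is conditional. If 164 is right, 25% are lost and only completers count, power is about 86% instead of 90%, given k of about 0.57, a two-sided 5% test and 1:1 allocation. With the planned offset it lies between about 88% and 92% if those lost average 1 to 6 months of follow-up. A shortfall in the primary analysis is thus possible but not shown. The statement still has to be corrected, because the trial's power claim rests on it.

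**What to change.** Go back to the original sample-size calculation and correct whichever figure is wrong.

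- If 164 is right, either state that 194 allows for about 15% attrition, or keep 25%, state that about 145 completers are expected, and give the power recalculated from the dispersion actually used in planning. Credit partial follow-up only if that was the basis of the calculation.
- If the evaluable number was meant to be about 146, correct the 164.

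In each case give the planning dispersion beside the figure. The value of 0.57 used here is a back-calculation and should not be printed as the design value. The cost is a sentence or two of correction, and possibly a less favourable attrition allowance or power figure. No extra participants and no change to design or analysis are required.

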### Study settings and participants

#### Study sites

Our current study sites are across three countries: Australia, Malaysia and the Philippines. The Australian sites are Queensland Children’s Hospital (Brisbane), Mater Hospital (Brisbane), Concord Repatriation Hospital (Sydney), Perth Children’s Hospital (Perth), Royal Darwin Hospital (Darwin) and Gold Coast University Hospital (Gold Coast). The Malaysian site is the University of Malaya Medical Centre (Kuala Lumpur) and in the Philippines, children are recruited from St Luke’s Hospital (Quezon City). Adults are recruited only from the Mater and Concord Repatriation Hospitals.

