### For the secondary aims

The change (12 months minus baseline) in (1) respective domain scores of the QoL tools and (2) spirometry values (FEV_1_ %predicted, FVC %predicted and FEV_1_/FVC) between treatment arms will be analysed using ANCOVA (analysis of covariance) and presented as the mean difference (95% CI). A Kaplan-Meier curve will be constructed for each group (intervention vs respective controls) for the time-to-the next exacerbation and respiratory-related hospitalisation, and an HR (using a Cox regression model) will be performed and reported.^18 19^

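### The 90% power claimed for QoL holds only for one standardised score combined across the child and adult tools, but the stated analysis takes each tool's own domain scores

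*Protocol article*

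**What the plan says.** Under *Outcomes and endpoints*, adults are assessed with the B-QoL, for which a respiratory subdomain is mentioned, and children with the parent-proxy PC-QoL. Each age group therefore has its own instrument.

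Under *Sample size*, the PC-QoL is given a minimal important difference of 0.9 with SD 1.8. The corresponding difference for the "adult B-QoL tool is domain dependent (7–10) (SD 17"). The section then claims: "With the standardisation of the scales, we will have 90% power to detect a difference of means between groups of 0.5 SDs". The evaluable number appears in the primary-outcome calculation: "if we obtain final endpoint data from 164 persons". The section concedes that the remaining secondary outcomes are not adequately powered.

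Under *For the secondary aims*, the QoL analysis is an ANCOVA of the change from baseline to 12 months in the "respective domain scores of the QoL tools", reported as a mean difference with 95% CI.

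Under *Study sites*, "Adults are recruited only from the Mater and Concord Repatriation Hospitals". The article does not say how many of the participants are expected to be adults.

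**The concern.** The power statement and the analysis statement describe different comparisons. The power statement relies on standardising the scales, which is what allows a parent-proxy cough score and an adult bronchiectasis score to enter one test. The analysis statement takes each tool's domain scores separately. That gives one comparison among the children and one or more domain comparisons among the adults, each on part of the sample.

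QoL is the only secondary outcome for which power is claimed, and the discussion of outcome choice places it beside exacerbations as a main outcome. If the by-tool analysis is run as stated, a null adult result could be read as coming from a test with 90% power when its real power may be well under half.

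**Working it through.** **Inputs.** From *Sample size*: target difference 0.5 SD, stated power 90%, 164 people with endpoint data. Alpha of 0.05 is stated there for the primary outcome only ("we will have 90% power (alpha=0.05) to detect a 40% reduction in the respiratory exacerbation rate"). I assume the same alpha for QoL, a two-sided test and equal arms. The adult share is not given and is varied from 10% to 50%.

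**Formula.** For N people in two equal arms and a standardised difference d, the two-sample t-test has noncentrality d × √N / 2 on N − 2 degrees of freedom. Power is the probability that |T| exceeds the two-sided 5% critical value.

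**Reproducing the plan's figure.** With all 164 in one comparison, noncentrality is 0.5 × √164 / 2 = 3.20 and power is 88.9% (89.3% by the normal approximation). This agrees with the stated 90%. Reaching 90% takes 85 per arm, 170 in total. The claim is therefore reproduced when every completer, child and adult, enters one standardised comparison.

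**By tool, no baseline adjustment.** A test on one tool also needs 170 people for 90% at 0.5 SD, which is more than the whole evaluable sample. So neither tool reaches 90% at any split. With 25% adults there are 123 children (noncentrality 0.5 × √123 / 2 = 2.77, power 78.5%) and 41 adults (0.5 × √41 / 2 = 1.60, power 34.5%).

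**By tool, with baseline adjustment.** I treat the stated SDs as those of the 12-month score and assume a baseline correlation r. The residual SD is then multiplied by √(1 − r²), and d becomes 0.5 / √(1 − r²): 0.577 at r = 0.5 and 0.700 at r = 0.7.

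Power in %, children / adults, N = 164:

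| Adult share (assumed) | Unadjusted | r = 0.5 | r = 0.7 |
|---|---|---|---|
| 10% | 85.5 / 15.7 | 93.6 / 19.4 | 98.8 / 26.3 |
| 20% | 81.1 / 28.4 | 90.7 / 36.0 | 97.8 / 49.3 |
| 25% | 78.5 / 34.5 | 88.8 / 43.8 | 97.1 / 58.9 |
| 40% | 69.0 / 51.4 | 80.9 / 63.4 | 93.0 / 79.7 |
| 50% | 60.9 / 60.9 | 73.3 / 73.3 | 87.9 / 87.9 |

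The larger group can be brought to about 90% at r near 0.5 when three quarters or more are children. The smaller group stays below 90% throughout the table, up to r = 0.7.

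**The case against.** The strongest reply is that a journal article is condensed. Its one sentence on secondary analyses covers QoL and spirometry together, it promises a detailed statistical analysis plan, and it refers to a supplement on outcomes. Standardisation is mentioned, so a combined analysis may well be intended and specified elsewhere. This stands in part. A reader might infer that the combined score will never be analysed, and the article does not support that. It shows only that no such analysis is described and that the one described is different. The point remains because it is not an omission: the article states both a power basis and an analysis, and they do not fit together. That the power claim means pooling is itself an inference, but standardising serves to put the two tools on a common scale, and the 90% needs the full sample.

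Three further readings are tempting and should not be made.

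- **That 0.5 SD conflicts with the stated important differences.** It equals the child tool's value (0.9 / 1.8 = 0.50) and is the midpoint of the adult range (7/17 = 0.41 to 10/17 = 0.59; 8.5/17 = 0.50).
- **That 90% should be restated as 89%.** The gap is rounding. A baseline correlation of 0.2 raises d to 0.5 / √0.96 = 0.510, and power for the combined score to 90.1%.
- **That both by-tool tests must fall short.** The planned ANCOVA, if it adjusts for baseline, could bring the larger group's test to 90%. The article claims no such gain, and it would not bring the smaller group's test to 90% at correlations up to 0.7.

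The attrition arithmetic ("To account for a 25% attrition loss, we will enrol a total of 194 people", although 164 / 0.75 = 219) is a separate issue. The figures here use the plan's own 164.

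**Conclusion.** The point holds as a contradiction between two statements in the article. The 90% power belongs to one comparison of a standardised score across both tools. The analysis stated for QoL is by tool and does not have that power, at least for the smaller group. Without baseline adjustment neither tool reaches 90% at any split. With 20–25% adults, the adult test has about 28–35% power unadjusted, 36–44% at r = 0.5 and 49–59% at r = 0.7.

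That the combined analysis gives about 89% at 164 is firm, given a two-sided 5% test and equal arms. The size of the loss by tool is a range, because the adult share and the baseline correlation are assumptions. The primary endpoint is not affected. This should be corrected before the final analysis, but it does not threaten the trial's main conclusion.

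**What to change.** Make the two sections agree, in one of two ways.

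(a) In the secondary-aims section, name as the powered QoL analysis one ANCOVA on a standardised score combined across tools: the PC-QoL and one named B-QoL domain, such as the respiratory domain. Each could be divided by its planning SD (1.8 and 17), with adjustment for standardised baseline and for tool or site. Report tool-specific domain results as supportive. The estimate is in SD units and mixes a parent-proxy cough score with an adult domain score, so the tool-specific results should be shown beside it.

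(b) Keep the by-tool analysis, and replace the single 90% figure with power per tool, using the expected numbers of children and adults and stating any baseline correlation relied on.

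Either option costs only wording in the protocol and the analysis plan; (a) adds one derived variable. No new data are needed, and the article says the analysis plan is still to be approved before the final analysis.

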#### Trial oversight

The study is being monitored by an iDMC. The iDMC meets every 4–6 months; its frequency is deemed by the members. The trial is overseen by the chief investigators of the grant (listed below). It is sponsored and monitored by the Queensland University of Technology (Brisbane, Australia).

#### Patient and public involvement

The grant submission was informed by both patient and public consultation. The formal research team and the original successful Australian Medical Research Future Funds grant applicants include a parent of a child with bronchiectasis. The study design was presented to and discussed with our First Nations advisory group (https://crelungs.org.au/cre-first-nations-advisory-group) and parent and community advisory group (https://crelungs.org.au/cre-parent-and-community-advisory-group) prior to submission of our grants. After we obtained our grant, our knowledge transfer plan was codesigned with the assistance of both advisory groups. This RCT is also part of the suite of studies within our Centre of Research Excellence^47^ funded by the Australian NHMRC whereby parents and patients inform our translational research.

## Discussion

As few RCTs target people with bronchiectasis, current pulmonary management is largely extrapolated from CF-based studies.^2 16 17^ Given the different pathobiological mechanisms between these conditions, there is a risk that some therapies beneficial for people with CF might have little benefit, or worse be detrimental to people with bronchiectasis, as shown by dornase-alfa in those with idiopathic bronchiectasis.^7 48^ Our RCT tests a therapeutic agent based on a sound scientific rationale and addresses some of these unmet needs by employing a novel mucoactive agent (erdosteine).^30^

Our RCT focuses on children and young adults for several important reasons: (1) intervening in early disease may arrest disease progression^1 7 49^ and (2) to limit the heterogeneity of bronchiectasis (by not including older adults who can have different underlying aetiologies and more comorbidities). Importantly, radiographic bronchiectasis in children (likely also in young adults) is reversible if treated early, thereby avoiding the later progressive decline in lung function.^7 49 50^ In contrast, adults with bronchiectasis symptoms from childhood have worse disease and poorer prognosis (c.f. adult-onset bronchiectasis).^51^ Thus, focusing on a younger age group will likely provide a greater impact on reducing future disease burden.

### Choice of study outcomes

Choosing outcomes that are both valid and consumer-informed is important. Respiratory exacerbations and QoL as our main outcomes were chosen when developing our study plan as they were considered the most important from the consumer perspective.^13 52^ Also, these are two of the key core outcomes for children with bronchiectasis.^52^ Furthermore, the published literature shows respiratory exacerbations have major negative health impacts on people with underlying lung diseases. In children with bronchiectasis, respiratory exacerbations are particularly important clinically as they are associated with increased psychological stress, impaired QoL, lung function decline (−1.9 FEV_1_% predicted per hospitalised respiratory exacerbations) and substantial healthcare costs.^23 53^ Moreover, each child hospitalised in Brisbane, Australia with an acute exacerbation of their bronchiectasis cost the public health system in 2016 $A30 182 (US$22 407; £16 642 and €20 397).^53^ Thus, we chose respiratory exacerbation rate as our RCT’s primary endpoint.

Our other secondary outcomes (hospitalisation, lung function) are also important from both consumer and clinical perspectives, as voted on by parents of children with bronchiectasis.^2^ However, our sample size may have limited power to detect a significant difference between groups for these outcomes.

We used the standard definitions to identify acute exacerbations for determining our primary outcome, in line with current ERS guidelines for bronchiectasis,^2^ and for defining exacerbations^3^ in children. For adults, we used the adult consensus definition.^24^

